### Exclusion criteria

Patient unable to provide consent (due to cognitive incapacity or lack of English proficiency)Volar angulationDiaphyseal extensionPartial articular fractures (AO/OTA 23B)Associated fracture or dislocation in any other body part that will affect the use of the involved wrist (ulnar styloid fracture will be permitted, as these are usually associated with the fracture under investigation)Open injuryPrevious wrist fracture on the same sideMedical condition precluding anaesthetic

### Intervention group

Surgical fixation using a volar locking plate was performed within 2 weeks of the initial injury according to the usual protocol of the participating institution, with an orthopaedic surgeon in attendance. This is a commonly performed procedure. Surgical technique and type of plate (make and length) was as per surgeon preference. A plaster cast was applied post-operatively but for no longer than 2 weeks. Active finger movement was encouraged post-operatively. Participants were reviewed 2 weeks (10–17 days) after surgery; the wound was reviewed and sutures removed where necessary. Participants were provided with a post-operative home-exercise programme (printed information). Referral for outpatient rehabilitation was not routinely provided but was permitted.

### Control group

Participants in this group were treated with a closed-reduction and cast immobilisation, avoiding wrist flexion, within 2 weeks of the initial injury. This method of casting is consistent with standard casting practice in Australia. Immobilisation of a distal radius fracture in flexion has been associated with an increased risk of fracture displacement as well as finger and metacarpophalangeal joint stiffness [23]. Also, immobilisation in a cast that is too restrictive and excessively flexed has been associated with an increased risk of complex regional pain syndrome (CRPS) [24, 25]. The reduction was performed in the emergency department under sedation and local anaesthetic infiltration into the fracture (haematoma block) where possible or in an operating room (if not possible in the emergency department). The procedure was performed by an orthopaedic surgeon or registrar. Post-reduction radiographs were taken to assess the fracture alignment. The best reduction achievable was accepted. The cast was removed at 6 (± − 1) weeks from the initial reduction. Active finger movement and light use of the hand was encouraged immediately. Participants were provided with a home-exercise programme (written information). Referral for outpatient rehabilitation was not routinely provided but was permitted.

### Patient and public involvement

The Consumer Advisory Group of ANZMUSC (the Australian and New Zealand Musculoskeletal Clinical Trials Network) reviewed the protocol and the study was endorsed by ANZMUSC. Separately, three elderly patients with wrist fracture (who were not study participants) were interviewed and provided feedback on what post-treatment information was most relevant and important to older patients with wrist fracture.

### Randomisation and allocation

Randomisation occurred immediately after consent was gained by the recruiting orthopaedic team, within 1 week of the date of the injury. The orthopaedic team member contacted a central computer-based randomisation service by telephone. Participants were randomised using the method of minimisation. Randomisation was stratified by site, and minimisation, adjusting for gender and age (60–74 years and > 74 years), was employed as recommended by the National Health and Medical Research Centre (NHMRC) Clinical Trials Centre which provided the randomisation service.

Given the nature of the comparisons (surgery versus no surgery), it was not possible to blind the surgeon (study) investigators or participants. While this increases the risk of performance and detection bias, every effort was made to ensure that treatment, other than the interventions under study was otherwise identical in both groups. The primary outcome (PRWE score at 12 months) was collected from participants by blinded researchers, by telephone.

The statistician and the investigators conducting the analysis will remain blinded to the treatment groups. The dataset will be de-identified and treatment allocation will be masked using dummy group names (for example, Group A and Group B). De-identification and masking will be performed by an independent investigator who is not associated with the analysis. Masking of treatment allocation will be maintained until the statistical analysis and interpretation has been completed and two versions of the manuscript have been prepared and agreed to by all authors.

### Data collection

Outcomes are collected at four timepoints; baseline, 3 months, 12 months and 24 months. The timepoints and corresponding outcomes are listed in Table 1. Baseline data is collected by the recruiting clinicians following consent. Baseline data includes age, gender, fracture type (AO/OTA 23A OR 23C), radiographic features of fracture, fracture-healing risk factors (see co-morbidities in Tables 2 and 3) and treatment preference. Paper-based data collection is forwarded to the study coordinator for direct electronic data entry into a central electronic database – REDCap™ [26].

**Table 1 Tab1:** Study outcomes

Baseline measure		Randomised	
		Surgical (*n*=__)	Non-surgical (*n*=__)
Age (years), mean (range)			
Gender n (%)	Female		
	Male		
Fracture type n (%)	23A		
	23C		
Radiographic features, mean (SD)	Dorsal angulation (degrees)		
	Radial tilt (degrees)		
	Ulnar variance (mms)		
	Articular step (mms)		
Co-morbidities, n (%)	Diabetes? (Y/N)		
	Smoker? (Y/N)		
	Glucocorticoid treatment? (Y/N)		
	Osteoporosis treatment? (Y/N)

**Table 2 Tab2:** Baseline characteristics for the randomised group

Baseline measure	Randomised	
	Surgical (*n* = __)	Non-surgical (*n* = __)
Age (years), mean (range)		
Gender *n* (%)		
Female		
Male		
Fracture type *n* (%)		
23A		
23C		
Radiographic features, mean (SD)		
• Dorsal angulation (degrees)		
• Radial tilt (degrees)		
• Ulnar variance (mm)		
• Articular step (mm)		
Co-morbidities, *n* (%)		
• Diabetes? (Y/N)		
• Smoker? (Y/N)		
• Glucocorticoid treatment? (Y/N)		
• Osteoporosis treatment? (Y/N)		

*SD* standard deviation

**Table 3 Tab3:** Baseline characteristics for the observational group

Baseline measure		Observational	
		Surgical (*n*=__)	Non-surgical (*n*=__)
Age (years), mean (range)			
Gender n (%)	Female		
	Male		
Fracture type n (%)	23A		
	23C		
Radiographic features, mean (SD)	Dorsal angulation (degrees)		
	Radial tilt (degrees)		
	Ulnar variance (mms)		
	Articular step (mms)		
Co-morbidities, n (%)	Diabetes? (Y/N)		
	Smoker? (Y/N)		
	Glucocorticoid treatment? (Y/N)		
	Osteoporosis treatment? (Y/N)		

Participants are followed up at 3 months post initial procedure (± 1 week), 12 months post initial procedure (± 1 month) and 24 months post initial procedure (± 1 month). There is an intention to collect outcomes at 5 and 10 years post treatment.

Participant follow-up at 3-month, 12-month and 24-month timeframes is conducted by telephone. The outcomes for the randomised arm of the study are collected by a blinded investigator. On rare occasions where data collection by telephone is not practical or possible (hearing impairment, English language proficiency), paper questionnaires are sent by post or by email to the participant to be completed and sent back to the research institution by reply-paid post. Completed telephone and postal questionnaires are entered into the password-protected central electronic database and paper-based records are collected and securely stored within the administering institution.

### Outcome variables

The primary outcome is the patient-rated wrist evaluation (PRWE) questionnaire at 12 (± 1) months post injury. The PRWE is a 15-item patient-reported measure of pain and function, specific to the wrist. It is a continuous score on a scale from 0 to 100 with higher scores indicating poorer outcomes [27]. It is commonly used, was developed with patient input and has been validated for use in patients with distal radius fractures [28].

Secondary outcomes include:
PRWE gathered at 3 months and 2, 5 and 10 yearsDisability of Arm, Shoulder and Hand (DASH) questionnaire at 12 months. The DASH is a 30-item patient-reported measure of disability and symptoms of the upper limb. It is a continuous score on a scale from 0 to 100 with higher scores indicating poorer outcomes [29]The EuroQol five-dimension five-level questionnaire (EQ-5D-5L), measuring health-related utility-based quality of life at 3 and 12 months and 2, 5 and 10 years. The EQ-5D-5L is a five-dimension patient-reported measure of health-related quality of life (HRQoL) with a separate visual analogue scale (VAS). Distributions of responses to each dimension can be reported categorically; it also produces two continuous variables, a EQ-utility index (EQ-UI) score and a EQ-VAS score. The EQ-UI score is scored on a scale of 0, equating to a health state equivalent to death and 1 equating to full health; it can also take negative values. Given that there are no published Australian normative data on which to calculate EQ-UI scores, UK norms will be used instead. The EQ-VAS score ranges from 0 to 100 with 0 equating to the worst health state imaginable and 100 equating to the best health state imaginable [30]Wrist pain using the numerical rating scale (NRS) at 3 and 12 months and 2, 5 and 10 years. The NRS is a patient-reported 11-point pain scale ranging from 0 to 10 with 0 equating to no pain and 10 equating to the worst possible painPatient-reported treatment success (at 12 months and 2, 5 and 10 years, 5-point Likert scale). The treatment success scale is a non-standard scale. See Additional file 1Patient-rated bother with appearance (at 12 month and 2, 5 and 10 years, 5-point Likert scale). The treatment success scale is a non-standard scale. See Additional file 1Complications (including deep infection, reoperation, neuropathy, tendon irritation requiring treatment, tendon rupture, fracture non-union at 6 months, implant failure, complex regional pain syndrome, death) at 3 months, 12 months, 2, 5 and 10 yearsRadiographic measures (ulnar variance, dorsal angulation, radial tilt, articular step) measured at presentation, post reduction, and between 6 weeks and 12 months)Therapy utilisation up to 3 months (Yes/No) and continuing at 3 months (Yes/No)

### Adverse events

Adverse events are defined as symptomatic fracture non-union (three of four cortices not united radiographically at a minimum of 6 months), infection (local infection requiring any treatment), neuropathy, tendon irritation (requiring treatment), tendon rupture or complex regional pain syndrome (diagnosed according to the International Association for the Study of Pain (IASP) clinical diagnosis criteria [31]).

### Study hypotheses

The primary hypothesis is that patients aged 60 years and older with displaced fractures of the distal radius managed surgically using volar-locking-plate fixation will have a clinically important superior patient-rated pain and function (PRWE score) at 12 months post injury compared to those managed non-surgically with closed reduction and plaster casting. A difference of greater than 14 points will be considered to be clinically important [32].

The secondary hypothesis is that patients aged 60 years and older with displaced fractures of the distal radius managed surgically using volar-locking-plate fixation compared to those managed non-surgically with closed reduction and plaster casting, will have:
Significantly lower rates of major complications (including deep infection, reoperation, neuropathy, tendon irritation requiring treatment, tendon rupture, fracture non-union, and implant failure, complex regional pain syndrome, death) at 3 and 12 months post treatmentSuperior (closer to normal) radiographic outcomes (ulnar variance and articular step (millimetres), dorsal angulation and radial tilt (degrees)) at post reduction and 6 weeks or moreSuperior PRWE scores at 3 months, 2, 5 and 10 years to a level of clinical importanceSuperior DASH scores at 12 months, to a level of clinical importance. A difference of greater than 11 points will be considered to be clinically important [33]Superior health-related quality of life (EQ-UI and EQ-VAS scores at 3 months and 12 months, 2, 5 and 10 years to a level of clinical importance. A difference of greater than 0.1 points in the EQ-UI score has previously been used as the minimal clinically important difference (MCID) in orthopaedic surgery [34] and musculoskeletal [35] contexts and will be considered to be clinically important. A difference of 10 on the EQ-VAS has been reported as the MCID and will be considered to be clinically important [36]Lower patient-reported pain (numerical rating scale NRS) at 3 months and 12 months, 2, 5 and 10 years to a level of clinical importance. A systematic review on the MCIDs of Visual Analogue Scales (VAS) used for assessment of acute pain reported that the median MCID was 17 mm on a 100-mm scale [37]. Given that the NRS uses whole integers between 0 and 10, a value of 2 points or greater will be considered to be clinically importantSuperior patient-reported treatment success at 12 months, 2, 5 and 10 years (measured on a 5-point Likert scale)Less patient-rated bother with appearance at 12 months, 2, 5 and 10 years (measured on a 5-point Likert scale)Lower therapy utilisation up to and at 3 months as measured by the prevalence of therapy utilisation at 3 months

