### Inclusion criteria

Age 60 years or olderDisplaced distal radius fracture, classified according to the Association for the Study of Internal Fixation/Orthopaedic Trauma Association (AO/OTA) [22] 23A (extra-articular distal radius fracture) or 23C (complete articular distal radius fracture). Displacement parameters include more than 10° dorsal angulation, referenced off a line perpendicular to the shaft of the radius or more than 3 mm shortening or more than a 2-mm articular step prior to reductionMedically fit for surgeryIndependent living (including hostel accommodation)Low-energy injury (fall from less than 1 m)Available for follow-up for 12 months

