### Statistical analysis

#### Analysis principles

Data will be analysed using statistical analysis package SAS (SAS Institute Inc., Cary, NC, USA) and R statistical computing software [40].

Recruitment for CROSSFIRE concluded in January 2019. The final analysis will commence after the 12-month data collection is complete. The de-identified data-set will be inspected for missing data and data quality.

Study outcomes produce both continuous and categorical data. Continuous data will be inspected for normality. Continuous data will be presented by mean values and standard deviations (SDs) as well as mean difference (MD) and 95% confidence interval (CIs) (see Tables 4 and 5 as examples) if normally distributed, otherwise by median and interquartile range.

**Table 4 Tab4:** Secondary outcomes at 3 months for the randomised group

Outcome		Randomised		
		Surgical (*n*=__)	Non-surgical (*n*=__)	MD (95%CI) or odds ratio (95%CI)
PRWE, mean (SD)				
ED-5D-5L, mean (SD)	EQ-UI			
	EQ-VAS			
Pain on NRS (0-10)				
Patient-reported treatment success n(%)	Very successful			
	Successful			
	Neutral			
	Unsuccessful			
	Very unsuccessful			
Therapy utilisation up to 3 months (Yes/No) n(%)				
Therapy utilisation at 3 months (Yes/No) n(%)				
Radiographic measures, mean (SD)	Dorsal angulation (degrees)			
	Radial tilt (degrees)			
	Ulnar variance (mms)			
	Articular step (mms)

**Table 5 Tab5:** Secondary outcomes at 3 months for the observational group

Outcome		Observational		
		Surgical (*n*=__)	Non-surgical (*n*=__)	MD (95%CI) or odds ratio (95%CI)
PRWE, mean (SD)				
ED-5D-5L, mean (SD)	EQ-UI			
	EQ-VAS			
Pain on NRS (0-10)				
Patient-reported treatment success n(%)	Very successful			
	Successful			
	Neutral			
	Unsuccessful			
	Very unsuccessful			
Therapy utilisation up to 3 months (Yes/No) n(%)				
Therapy utilisation at 3 months (Yes/No) n(%)				
Radiographic measures, mean (SD)	Dorsal angulation (degrees)			
	Radial tilt (degrees)			
	Ulnar variance (mms)			
	Articular step (mms)			

Categorical data will be summarised according to frequency (*n*) and incidence (%) (see Table 5). Comparison between treatment groups will be tested using chi-squared and odds ratio with 95% CI.

Comparisons between treatment groups will be tested at the two-sided, 5% significance level. *P* values will be reported to three decimal places if *P* > 0.001. *P* values < 0.001 will be reported as < 0.001. Means and SDs will be reported to one decimal place.

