### Secondary analysis

Outcomes for the randomised group and the observational group will be analysed and represented separately. Outcomes gathered at 3 months will be displayed for the randomised group (see Table 4) and for the observation group (see Table 5). Outcomes gathered at 12 months will be displayed for the randomised group (see Table 6) and for the observational group (see Table 7). Continuous outcomes will be reported by mean values as well as the MDs and 95% CIs. Categorical outcomes will be reported by frequency, incidence and odds ratios.

**Table 7 Tab7:** Primary and secondary outcomes at 12 months for the observational group

Outcome		Observational		
		Surgical (*n*=__)	Non-surgical (*n*=__)	Mean difference (95%CI)
PRWE				
DASH				
ED-5D-5D, mean (SD)	EQ-UI			
	EQ-VAS			
Pain on NRS (0-10)				
Patient-reported treatment success n(%)	Very successful			
	Successful			
	Neutral			
	Unsuccessful			
	Very unsuccessful			
Patient-reported bother with appearance n(%)	Not at all			
	Bothered a little			
	Bothered moderately			
	Very bothered			
	Extremely bothered			
Radiographic measures, mean (SD)	Dorsal angulation (degrees)			
	Radial tilt (degrees)			
	Ulnar variance (mms)			
	Articular step (mms)			

The MDs of PRWE measured at 3 months between the surgical and non-surgical groups will be tested using two-sample *t* tests. The MDs of DASH measured at 12 months between the surgical and non-surgical groups will be tested using two-sample *t* tests.

Physical therapy utilisation up to and at 3 months will be analysed. If surgical treatment is shown to be superior, a cost-effectiveness analysis will be conducted incorporating therapy utilisation and published separately to this analysis. For the purpose of this analysis, therapy utilisation up to 3 months (Yes/No) and ongoing therapy utilisation at 3 months (Yes/No) will each be reported in terms of frequency, incidence and odds ratio between each treatment group. See Tables 3 and 4 as examples.

Complications will be reported in terms of frequency, incidence and the odds ratio between each treatment group (see Tables 8 and 9 as examples). Odds ratio will be calculated based on the number of participants for whom data is available.

**Table 8 Tab8:** Complications for randomised group

Complication; frequency (incidence)	Randomised group		
	Surgical (*n* = _)	Non-surgical (*n* = _)	Odds ratio (95% CI)
Deep infection	*n* (%)	*n* (%)	
Reoperation	*n* (%)	*n* (%)	
Neuropathy	*n* (%)	*n* (%)	

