Tendon irritation requiring treatment	*n* (%)	*n* (%)	
Tendon rupture	*n* (%)	*n* (%)	
Fracture non-union at 6 months	*n* (%)	*n* (%)	
Implant failure	*n* (%)	*n* (%)	
CRPS	*n* (%)	*n* (%)	
Death	*n* (%)	*n* (%)	
Any complications	*n* (%)	*n* (%)	

*CI* confidence interval, *CRPS* chronic regional pain syndrome

**Table 9 Tab9:** Complications for observational group

Complication; frequency (incidence)	Randomised group		
	Surgical (*n* = _)	Non-surgical (*n* = _)	Odds ratio (95% CI)
Deep infection	*n* (%)	*n* (%)	
Reoperation	*n* (%)	*n* (%)	
Neuropathy	*n* (%)	*n* (%)	
Tendon irritation requiring treatment	*n* (%)	*n* (%)	
Tendon rupture	*n* (%)	*n* (%)	
Fracture non-union at 6 months	*n* (%)	*n* (%)	
Implant failure	*n* (%)	*n* (%)	
CRPS	*n* (%)	*n* (%)	
Death	*n* (%)	*n* (%)	
Any complications	*n* (%)	*n* (%)	

*CI* confidence interval, *CRPS* chronic regional pain syndrome

Repeated measures analysis will be used for the following:
Continuous variables measured at 3 months and 12 months include EQ-5D-5L (UI and VAS scores), pain on NRS (0–10) and radiographic measures (dorsal angulation, radial tilt, ulnar variance and articular step). These measurements will be analysed using analysis of variance (ANOVA) with repeated measuresCategorical variables measured at 3 months and 12 months include patient-reported treatment success (Likert) and patient-reported bother with appearance (Likert). See Additional file 1 for question format. These variables will be analysed by contingency table to compare the frequency of treatment success categories between the two randomised groups. Results will be displayed as odds ratio with 95% CIs (see Table 4 for example)

The observational group will be used to investigate potential selection bias. Baseline characteristics will be compared between the observational group and the randomised group (see Table 10 for example).

**Table 10 Tab10:** baseline characteristics for the randomised and observational arms of trial

Baseline measure		Randomised arm (*n*=__)	Observational arm (*n*=__)
Age (years), mean (range)			
Gender n (%)	Female		
	Male		
Fracture type n (%)	23A		
	23C		
Radiographic features, mean (SD)	Dorsal angulation (degrees)		
	Radial tilt (degrees)		
	Ulnar variance (mms)		
	Articular step (mms)		
Co-morbidities, n (%)	Diabetes? (Y/N)		
	Smoker? (Y/N)		
	Glucocorticoid treatment? (Y/N)		
	Osteoporosis treatment? (Y/N)		

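### The radiographic hypothesis is about closeness to normal, but for three of the four measures the planned test compares raw values and does not measure closeness

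*SAP article*

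**What the plan says.** Study hypotheses lists, among the secondary hypotheses, that surgery will give superior radiographic results, glossed as "closer to normal) radiographic outcomes (ulnar variance and articular step (millimetres), dorsal angulation and radial tilt (degrees", after reduction and at 6 weeks or more.

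The analysis sections work on the measurements as recorded:

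- Secondary analysis (repeated measures): "radiographic measures (dorsal angulation, radial tilt, ulnar variance and articular step). These measurements will be analysed using analysis of variance (ANOVA) with repeated" measures.
- Secondary analysis (reporting): "Continuous outcomes will be reported by mean values as well as the MDs and 95% CIs".
- The shells of Tables 4 to 7 and 11 to 13 carry a row block headed "Radiographic measures, mean (SD"), with a mean-difference column.
- Analysis principles: data that are not normally distributed are summarised "otherwise by median and interquartile range", which is again a summary of the raw value.

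Inclusion criteria gives the only measurement convention in the document: displacement may be shown by "more than 10° dorsal angulation, referenced off a line perpendicular to the shaft of the radius". No normal value, deviation variable, acceptable-alignment category or direction rule appears for any radiographic measure.

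**The concern.** Closeness to normal is a distance. A raw mean is a location. The two agree when every wrist departs from normal in the same direction. They part company when some wrists lie on one side and some on the other, because opposite deviations cancel in the mean.

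For PRWE and DASH, Outcome variables says that higher scores are worse, so a mean difference has a direction and answers the question. For the radiographs the plan chose a hypothesis that is neither higher nor lower, then planned a comparison that can only show higher or lower. Dorsal angulation, radial tilt and ulnar variance can each fall on either side of a normal value. Articular step cannot be negative and its normal value is zero, so raw value and distance coincide.

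At stake is whether the reported result for these three measures can support or refute the stated hypothesis.

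**Working it through.** There is no radiographic figure in the plan to reproduce. The check is whether a test on raw values tracks a test on distance from normal.

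**Inputs from the document.** Two-sided 5% level (Analysis principles); 64 per group (Power and sample size).

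**Inputs assumed.** The deviation D from normal is taken as normally distributed with mean μ and SD σ in each group. All μ and σ are illustrative, because the document gives no radiographic means, SDs, normal values or sign convention.

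**Formula.** Mean distance from normal is the mean of a folded normal variable:

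E|D| = σ√(2/π)·exp(−μ²/2σ²) + |μ|·[1 − 2Φ(−|μ|/σ)]

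**Worked case, −6/5 v +3/5 (mean/SD, degrees).**

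- First group: 5 × 0.7979 × exp(−0.72) + 6 × (1 − 2 × 0.1151) = 1.94 + 4.62 = 6.56.
- Second group: 5 × 0.7979 × exp(−0.18) + 3 × (1 − 2 × 0.2743) = 3.33 + 1.35 = 4.69.
- Raw mean difference: −6 − 3 = −9.

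**Cancellation case, 0/1.5 v 0/3 (mm).** 1.5 × 0.7979 = 1.20 and 3 × 0.7979 = 2.39. Raw mean difference: 0.

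**Rejection rates** come from simulation, with Welch t tests at a single time point on the raw deviation and on its absolute value (20,000 trials for rows 2, 3 and 5; 4,000 for rows 1, 4 and 6).

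| Row | Group 1 v group 2 (mean/SD) | Raw difference | Raw test rejects | Mean distance from normal | Distance test rejects |
|---|---|---|---|---|---|
| 1 | 3/5 v 12/8 | −9 | about 100% | 4.7 v 12.5 | about 100% |
| 2 | 0/1.5 v 0/3 | 0 | 4.8% | 1.2 v 2.4 | 99.9% |
| 3 | 0/1.5 v 0/2.25 | 0 | 5.2% | 1.2 v 1.8 | 84.3% |
| 4 | −6/5 v +6/5 | −12 | about 100% | 6.6 v 6.6 | 5.3% |
| 5 | −6/5 v +3/5 | −9 | about 100% | 6.6 v 4.7 | not run |
| 6 | 4/3 v 0/12 | +4 | 73% | 4.3 v 9.6 | about 100% |

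**Reading the rows.**

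- Row 1: deviations mainly on one side. Both analyses agree in direction and significance.
- Rows 2 and 3: a real difference in closeness is missed, because the raw means are equal.
- Row 4: a large raw difference with no difference in closeness.
- Row 5: group 1 has the lower mean but lies further from normal. The result is reversed only for a reader who takes lower as better.
- Row 6: group 2's mean sits exactly at normal, so comparing group means with normal favours group 2, although group 1's wrists are on average less than half as far away.

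**The case against.** The strongest reply is that this population makes one-sided deviation likely. Purpose of the analyses restricts the study to dorsally displaced fractures, and Exclusion criteria rules out volar angulation. Control group says the best achievable reduction was accepted, so residual deviation in the cast arm would be expected mostly in the original direction. Row 1 is then the relevant case and nothing is lost. This stands as a limit on how likely the problem is, but it does not remove it. The exclusion applies at entry, whereas the hypothesis concerns alignment after treatment, when over-correction is possible. The displacement criteria are alternatives, so a patient can enter on shortening or articular step alone. Nothing comparable restricts ulnar variance or radial tilt.

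A second reply is that the adverse rows are assumed, and that they use single-time t tests where the plan has repeated-measures ANOVA. That is correct. They show what can happen, not what is likely. ANOVA on raw values still compares means, so the change of test does not restore distance.

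A third reply is that the table shells show mean (SD) by arm, so unequal spread or means on opposite sides of normal would be visible. This helps a careful reader, but without a stated normal value it does not turn the planned test into a test of the hypothesis.

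A fourth reply is that measurement conventions may sit in the full plan or the protocol, neither of which is shown. For conventions alone that would be enough. Here, however, the article itself states both the hypothesis and the quantity to be tested, and the two differ.

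A reader might also infer more than the text supports: that the plan specifies signed values, that it defines closeness wrist by wrist, or that it will count a lower mean dorsal angulation as better. It states none of these. It sets no sign convention, uses closer to normal as a gloss on superior, and tests two-sided with no direction rule. Recording unsigned angles would not cure the gap, since size from the perpendicular line equals distance from normal only if normal is zero.

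**Conclusion.** The point holds for dorsal angulation, radial tilt and ulnar variance: the planned comparison does not measure the stated hypothesis unless nearly all deviations lie on one side of normal. That condition is plausible for dorsal angulation and is not secured for any of the three.

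The size cannot be fixed from the document. Under the assumed values it ranges from no consequence (row 1), through a missed difference (rows 2 and 3), to a reversed one (rows 5 and 6). It would go too far to say that the trial will miss or reverse its radiographic result, because no radiographic data or SDs are given from which to judge how often deviations fall on both sides.

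The reach is one secondary hypothesis. Articular step is already on the right scale, and the primary PRWE analysis is untouched. The change is worth making because it is cheap and settles in advance what counts as normal.

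**What to change.** Before treatment groups are unmasked:

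1. Prespecify one reference value and one sign convention each for dorsal angulation, radial tilt and ulnar variance.
2. Derive each participant's absolute deviation from that value. Leave articular step as it is.
3. Make the between-group difference in mean absolute deviation, with a 95% CI, the test of this hypothesis. Use a robust or bootstrap interval if the deviations are skewed.
4. Keep the raw mean (SD) rows in Tables 4 to 7 and 11 to 13 as description.

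The cost is a short change of wording and one derived variable for each of the three measures, from data already collected. The downsides are that a reference value must be chosen in advance, and that absolute deviations are right-skewed and lose direction. The retained raw means supply the direction.
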